## Termination of the Trial

In the case of complete premature termination of the trial, participating investigators/subjects, and the Institutional Review Board must be promptly informed of the termination.

## Protocol Amendments

Alterations of the protocol may be made as the study progresses. Such changes will be captured in writing and will document the reasons for the change.

If any amendments need to be reviewed by ethical committee, it will be reviewed/approved prior to implementation.

# Safety Instructions and Guidance

As any ingredient in the test supplement is edible and generally recognized as safe, serious adverse event should not be expected to occur. However, if any adverse event will occur, it will be managed as described in this captor.

## Adverse Events and Laboratory Abnormalities

### Adverse Events

An adverse event (AE) is any untoward medical occurrence in a clinical investigation subject who has been administered a test supplement and which does not necessarily have a causal relationship with this treatment. An AE can be any unfavorable and unintended sign, symptom, or disease temporally associated with the use of a test supplement, whether or not it is considered related to that supplement. Pre-existing conditions which worsen during a study are to be reported as AEs.

During the study, subjects should record any adverse effects in their diary. At each visit the subject will be asked any difficulties or problems from the last visit. Any adverse events (AEs) will be documented and in the study record and will be classified according to the description, duration, intensity, frequency, and outcome. The investigator will assess any AEs and decide causality.

Intensity of AEs will be graded on a three-point scale (mild, moderate, severe) and reported in detail in the study record.

Mild: Awareness of event but easily tolerated

Moderate: Discomfort enough to cause some interference with usual activity

Severe: Inability to carry out usual activity

The causality relationship of test supplement to the adverse event will be assessed by the investigator as either:

Most probable: There is a reasonable relationship between the test supplement and AEs. The event responds to withdrawal of test supplement (dechallenge) and recurs with rechallenge when clinically feasible.

Probable: There is a reasonable relationship between the test supplement and AEs. The event responds to dechallenge.

Possible: There is a reasonable relationship between the test supplement and AEs. Dechallenge information is lacking or unclear.

Unlikely: There is a temporal relationship to the test supplement administration but there is no reasonable causal relationship between the test supplement and the AEs.

Not related: No temporal relationship to the test supplement administration or there is a reasonable causal relationship between non-test supplement, concurrent disease or circumstance and the AEs.

### Serious Adverse Event

A serious adverse event (SAE) is any experience that suggests a significant hazard, contraindication, side effect or precaution. It is any AE that results in any of the following outcomes:

- Death
- A life-threatening adverse event
- Hospitalization
- A persistent or significant disability or incapacity
- A congenital anomaly/birth defect in the offspring of a subject who received the study treatment
- Important medical events that may not be immediately life-threatening or result in death or hospitalization but may jeopardize the subject or may require intervention to prevent one of the outcomes listed above.

### Laboratory Test Abnormalities

The investigator must assess the clinical significance of all abnormal laboratory values as defined by the compendium of normal values for the reference laboratory.

Any treatment emergent abnormal laboratory result which is clinically significant, i.e., meeting one or more of the following conditions, should be recorded as a single diagnosis on the AEs form in the study record:

- Accompanied by clinical symptoms
- Requiring a change in concomitant therapy

This does not apply to any abnormal laboratory result which falls outside the laboratory reference range but which does not meet the clinical significance criteria or those which are a result of an AE which has already been reported.

Any laboratory result abnormality fulfilling the criteria for a serious adverse event (SAE) should be reported as such, in addition to being reported as an AE in the study record.

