## Labeling and Coding

The aluminum pouch containing the test supplement (for 30 days) will be labelled either A or B. A randomization will achieved by envelope containing a card printing either A or B at the enrollment. The sponsor keeps the key in a sealed envelope until the key open.

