### JKOM and JOA

Subjects will fill JKOM questionnaire by his/her own.

Orthopedist will fill JOA score list interviewing subject.

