## Laboratory Analysis

Blood and urine samples will be collected at Visit 1 and Visit 3.

The following parameters will be analyzed.

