### Plasma fatty acids

- arachidonic acid (AA)
- eicosapentaenoic acid (EPA)
- di-homo-γ-linoleic acid
- docosahexaenoic acid (DHA)

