### Urine

- Urine specific gravity
- pH

LSI Medience Corp (Tokyo, Japan) will be used in this study to measure laboratory parameters.

The total blood volume collected for the laboratory assessments listed above will be approximately < 20 mL at a study visit.

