# STATISTICAL EVALUATION

## Determination of sample size

Sample size is set according to the report by Maki et al. [6], in which the administration of krill oil (2 g/d for 4 weeks) showed significant differences in the plasma EPA & DHA concentrations of 25 participants in the control and krill oil groups.

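### The protocol has the investigator review all abnormal laboratory values and nowhere withholds the post-baseline fatty acids, which can identify the krill oil letter, until JOA scoring and per-protocol decisions are final

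*Protocol*

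**What the plan says.** **Panel.** Under Laboratory Analysis: "Blood and urine samples will be collected at Visit 1 and Visit 3". The listed parameters are blood count, serum tests, urine tests and, under Plasma fatty acids, AA, EPA, di-homo-γ-linoleic acid and DHA. The Urine section names an external laboratory that "will be used in this study to measure laboratory parameters". It does not say who receives the reports or when.

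**Review duty.** Under Laboratory Test Abnormalities the rule reads: "The investigator must assess the clinical significance of all abnormal laboratory values as defined by the compendium of normal values for the reference laboratory". No analyte is exempted. Follow-up of Laboratory Abnormalities adds that clinically significant unexplained values are to be repeated and followed.

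**Expected arm difference.** Determination of sample size relies on a cited krill oil study (2 g/d for 4 weeks) that "showed significant differences in the plasma EPA & DHA concentrations of 25 participants in the control and krill oil groups".

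**Code.** Under Labeling and Coding: "The aluminum pouch containing the test supplement (for 30 days) will be labelled either A or B". Allocation is by an envelope card bearing the same letter, and the sponsor holds the key sealed. Unblinding and Allocation Concealment deals only with emergency unblinding.

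**Rater.** Under JKOM and JOA: "Orthopedist will fill JOA score list interviewing subject". JKOM is completed by the subject. Both are primary outcomes.

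**The concern.** A double-blind trial that measures a marker of exposure to its own test product normally keeps post-baseline values of that marker away from the people who assess subjects. This protocol protects the key but not the marker. Read as written, the review duty extends to the four fatty acids whenever they are abnormal, so a site that looked at them would breach nothing.

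Two features raise the stakes. First, the code has only two letters for all 50 subjects, so learning what one letter means reveals the assignment of everyone already treated and everyone still to come. Second, several steps rest on judgement: the interview-based JOA score, adverse event causality, removal at the Qualified Investigator's discretion, and the undefined category of major protocol violations. Effectiveness is analysed in the per-protocol population, so exclusions act directly on the primary comparison, and the protocol states no point at which that population is fixed.

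**Working it through.** **1. Is the marker expected to separate the arms in this trial?** The cited study used 2 g/d for 4 weeks. Here the daily amount is 8 capsules × 250 mg = 2,000 mg = 2 g (Directions; Test supplements), for 30 days. Dose and duration therefore match the study that the protocol relies on for an EPA and DHA difference.

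**2. Does any section close the route?** Labeling and Coding protects the key. Unblinding and Allocation Concealment covers emergencies. Laboratory Analysis and its subsections say what is measured and by whom. Laboratory Test Abnormalities covers all abnormal values. None withholds, delays or redirects fatty acid results. The repeat-and-follow rule under Follow-up of Laboratory Abnormalities suggests that abnormal results reach the investigator while they can still be acted on, but it gives no timing.

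**3. What could be exposed?**
- A subject's own Visit 3 JOA: no. Blood is drawn at the same visit, so the result does not yet exist.
- JOA scores of later subjects: yes, through the shared letter, if results come back in time and reach the rater. Visit 1 lists randomization before the baseline assessments, so the baseline JOA of later subjects could be exposed as well as their Visit 3 JOA.
- Adverse event causality, discretionary removal and major-violation decisions: yes, if made after results are seen.
- JKOM: not through the rater, because the subject completes it.
- The 80% compliance rule: no, because it is a capsule count.

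**4. How many results would decode the letters?** The plan's figure of 25 per arm cannot be reproduced, because the sample size section gives no alpha, power, difference or SD. The standardised EPA or DHA difference d must therefore be assumed. Reading the cited result as 25 per group with two-sided alpha 0.05:
- just significant: d = 2.011 × √(2/25) = 0.57
- detectable with 80% power: d = (1.960 + 0.842) × √(2/25) = 0.79
- detectable with 90% power: d = (1.960 + 1.282) × √(2/25) = 0.92

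Larger values of 1 and 2 are added as further assumptions.

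Suppose the site held every value by letter and compared the two means after m completers per letter. The difference in means has expectation d and variance 2/m in SD units, so

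P(correct letter) = Φ(d × √(m/2)), and 95% requires m = 2 × (1.645/d)².

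- d = 0.57: 16.7, so 17 per letter
- d = 0.79: 8.7, so 9
- d = 0.92: 6.4, so 7
- d = 1: 5.4, so 6
- d = 2: 1.4, so 2

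All are below 25. Decoding before the last subject finishes is therefore arithmetically possible, provided enrolment is staggered and results are returned as they are produced.

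**The case against.** The strongest reply is that the protocol does not order the release of fatty acid results. It names a laboratory and stops there. The results may be batched at the end, and routing may be set in a laboratory instruction outside the protocol. The review duty covers abnormal values only, and the document does not say whether the four fatty acids have reference limits or whether krill oil would push subjects beyond them. The roles are also distinct on paper: an investigator, a Qualified Investigator and an orthopedist are named, and nothing says they are the same person. All of this stands, and it limits the point to a missing safeguard. It does not close the route, because the review duty is unqualified and no other section restricts it.

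Two stronger readings are tempting.

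- A reader might infer that EPA and DHA values are sent to the clinic subject by subject, so that the blind is in fact broken. The document states neither the recipient nor the timing.
- A reader might put a size on the JOA bias. Under fully sequential enrolment with immediate results, between 25 − 17 = 8 and 25 − 2 = 23 subjects per arm would remain unscored. Multiplying those shares by an assumed rater shift of 0.2 to 0.3 SD gives 8/25 × 0.2 = 0.06 to 23/25 × 0.3 = 0.28 SD. Neither the enrolment pattern, nor the turnaround, nor the rater shift, nor d is given. With compact enrolment or batched assays no later JOA is exposed and the bias is zero. The decoding formula also assumes that the site sees all values by letter, which is more than the review of abnormal values requires.

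**Conclusion.** The point holds as a gap in the blinding safeguards. The protocol expects plasma EPA and DHA to separate the arms, places them in the panel whose abnormal values the investigator must review, uses one trial-wide two-letter code, and has no rule keeping post-baseline fatty acid results from site staff.

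Harm requires two things that the document does not state: that results are returned while subjects are still being assessed, and that they reach the JOA rater or those making causality, removal and violation decisions. The size of any bias cannot be derived and may be zero. The figures of 2 to 17 completers per letter are an illustration under assumed standardised differences of 2 to 0.57, and only if all values are visible by letter. They show that the safeguard is worth having; they do not show that the blind fails. This is a cheap improvement that should be made.

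**What to change.** In Plasma fatty acids and Laboratory Test Abnormalities, state that the laboratory holds post-baseline results for EPA, DHA, AA and di-homo-γ-linoleic acid, or sends them only to a person with no subject contact, until three things are done: the last Visit 3 JOA is scored, the per-protocol population is fixed, and the database is locked. Exclude these four analytes from the investigator's review of abnormal values. All other blood, serum and urine tests continue to be reviewed as planned.

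The cost is a short addition to the protocol and a reporting instruction to the laboratory. Sample size and power are unaffected. The downside is that the site cannot see fatty acid values during the trial; the protocol gives them no specific role in subject management.

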## Treatment and Follow-up of AEs and Laboratory Abnormalities

### Treatment and Follow-up of AEs

AEs, especially those for which the relationship to the test supplement is suspected, should be followed up until they have returned to baseline status or stabilized.

If after follow-up, return to baseline status or stabilization cannot be established, an explanation should be recorded in the study record.

### Follow-up of Laboratory Abnormalities

In the event of clinically significant unexplained abnormal laboratory test values, the tests should be repeated and followed up until they have returned to the normal range and/or an adequate explanation of the abnormality is found. If a clear explanation is established, it should be recorded in the study record.

## Reporting of SAEs and Unexpected Adverse Reactions

The Qualified Investigator will be responsible for classification of an AE as an SAE within 24 hours of notification. Causality should be signed off by the Qualified Investigator prior to reporting to ethics and regulatory bodies. Notification of any serious adverse events must be made in writing to the study sponsor. The IRB will be notified of all SAEs and unexpected adverse reactions.

# STATISTICAL EVALUATION

## Determination of sample size

Sample size is set according to the report by Maki et al. [6], in which the administration of krill oil (2 g/d for 4 weeks) showed significant differences in the plasma EPA & DHA concentrations of 25 participants in the control and krill oil groups.

**8.2 Analytical Populations**

- The **Safety Population** will consist of all subjects who received any amount of either product, and on whom any post-randomization safety information is available.
- The **Per Protocol (PP) Population** “Per Protocol (PP) Population” consists of all subjects who consumed at least 80% of test or placebo doses do not have any major protocol violations and complete all study visits. Subject who has a compliance of <80% will be deleted from the further analysis.
  1. **Analysis Plan**

An effectiveness analysis based on the per protocol population will be performed. Continuous variables will be tested for normality and log-normality. Log-normally distributed variables will be analyzed in the logarithmic domain. Non-normal variables will be analyzed by appropriate non-parametric tests.

Missing values will be deleted in a pair-wise manner for the comparison, except in the structured questionnaires of JKOM (Q1 – 25) and JOA in which missing data will be deleted in a list-wise manner.

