**Removal by Qualified Investigator:**

Subject may be discontinued at the discretion of the Qualified Investigator. A subject leaving the study prematurely will not be replaced by another. Criteria for removal of subjects from the study will include:

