**Clinical reasons**

A subject may be withdrawn from the study if, in the opinion of the Qualified Investigator, it is not in the subject's best interest to continue. This includes but is not limited to adverse events related to the test supplement causing clinically significant illness, the need for prohibited concomitant medication or any participant who meets exclusion criteria during the trial. All serious adverse events will result in withdrawal from the trial. Participants who experience exacerbation of any current condition and require additional intervention or a change in their current intervention will be withdrawn from the trial.

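### The only planned efficacy analysis uses a per-protocol set formed after randomisation, so the krill oil–placebo comparison is not protected by randomisation; the size and direction of any bias are unknown.

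*Protocol*

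**What the plan says.** Protocol section 8.2 defines two populations. The Safety Population is "all subjects who received any amount of either product, and on whom any post-randomization safety information is available". The Per Protocol Population is "all subjects who consumed at least 80% of test or placebo doses do not have any major protocol violations and complete all study visits", and the same bullet adds: "Subject who has a compliance of <80% will be deleted from the further analysis".

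The Analysis Plan that follows assigns efficacy to the second set: "An effectiveness analysis based on the per protocol population will be performed". The Statistical tests paragraph gives the covariate-adjusted model for the primary outcomes and names no other set. Section 8.3.1 covers descriptive adverse-event reporting only. The Analysis Plan also drops JKOM and JOA records with missing data list-wise.

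Two rules under Early Withdrawal, Clinical reasons, bear on who can complete all visits: "All serious adverse events will result in withdrawal from the trial", and "Participants who experience exacerbation of any current condition and require additional intervention or a change in their current intervention will be withdrawn".

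**The concern.** Each condition for entering the efficacy set is determined after allocation and may depend on the product taken, on how the knee is doing, or on both. Compliance can reflect tolerability or perceived benefit. Withdrawal for an exacerbation that needs treatment can reflect the very symptom that JKOM and JOA measure. Once subjects are selected on such events, the two groups compared are no longer the groups that were randomised, and a difference between them need not be due to the supplement.

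The Introduction sets the objective as comparing krill oil with placebo for symptoms in adults with mild knee pain. The planned analysis addresses only compliant completers without a major violation. It also discards usable data: a subject with complete Day 1 and Day 31 scores can be excluded for missing Visit 2, or for taking fewer than 80% of the capsules.

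**Working it through.** **Step 1. Who leaves the efficacy set, by rule.** No stated figure is in dispute, so the sections are read together first.

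| Event after randomisation | Protocol section | Day 1 and Day 31 scores could still exist? | In efficacy set? |
|---|---|---|---|
| Compliance below 80% | 8.2 | Yes | No |
| Visit 2 missed (may be a phone call; no JKOM or JOA in Appendix 1) | 8.2, Visit 2, Appendix 1 | Yes | No, read literally |
| Major protocol violation | 8.2 | Yes | No |
| Serious adverse event | Clinical reasons, 8.2 | Only if followed after withdrawal | No |
| Exacerbation needing added or changed intervention | Clinical reasons, 8.2 | Only if followed after withdrawal | No |
| Worse JKOM or JOA, no change of intervention | – | Yes | Yes |

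The exacerbation rule covers any current condition. Every subject enters with knee pain (Inclusion Criteria), so it can include the knee.

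**Step 2. Size under stated assumptions.** From the protocol: 25 randomised per arm (Study Design). Assumed, because the protocol gives none of these: normal outcomes with SD 1, higher is better, unadjusted two-sided t test at 5%.

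*(a) Extreme one-arm selection, no true effect.* The k worst of 25 are removed from one arm and k at random from the other. The bias is minus the expected sum of the k lowest values, divided by 25 − k. Simulation of 40,000 trials per k:

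| k | Bias (SD) | Rejection rate |
|---|---|---|
| 2 | 0.15 | 9.4% |
| 3 | 0.22 | 13.3% |
| 5 | 0.34 | 23.1% |

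With the same one-arm selection but a correlation of only 0.3 between exclusion and outcome, rejection is 5.4%, 5.6% and 6.2% for k = 2, 3, 5. With a correlation of 0.5 it is 6.1%, 6.6% and 8.7%.

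*(b) Different exclusion rates by arm, no true effect.* Removing the worst fraction f of an arm raises its mean by φ(z_f)/(1 − f), where z_f is the normal quantile at f. For 20% against 0% this is 0.35 SD, with rejection 23%. For 20% against 10% it is 0.15 SD, with rejection 9%. For 10% against 10% there is no bias and rejection is 5.0%. Analysing all randomised subjects in the same simulated trials gave 4.7% to 5.3%.

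*(c) One outcome threshold in both arms.* Anyone below −1 SD leaves, whichever the arm. With no true effect, both arms shift equally: bias is about 0 and rejection about 5%. With an assumed true effect of 0.5 SD:
- placebo mean after exclusion: φ(1)/Φ(1) = 0.242/0.841 = 0.288
- krill mean after exclusion: 0.5 + φ(1.5)/Φ(1.5) = 0.5 + 0.130/0.933 = 0.639
- difference: 0.639 − 0.288 = 0.35 SD, which is smaller than the truth.

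*(d) Purely random exclusion.* There is no bias, only lost information. The effect detectable with 80% power (noncentral t) is 0.81 SD at 25 per arm and 0.91 SD at 20 per arm. Dropouts are not replaced ("A subject leaving the study prematurely will not be replaced by another"). That is no defect in itself, but the loss is not made good.

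**The case against.** The strongest reply is that blinding and identical rules in both arms limit differential exclusion. If krill oil affects nothing, compliance and withdrawals have the same distribution in each arm, and a per-protocol test keeps its 5% level, as (c) shows. This stands, and it rules out several stronger readings.

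- A reader might infer that any worsening removes a subject. The withdrawal rule requires exacerbation together with additional or changed intervention, so a subject whose scores merely decline stays in.
- A reader might infer a bias in favour of krill oil, or a type I error of 23%. That figure needs near-perfect selection on outcome in one arm and none in the other. Nothing in the protocol says exclusions would fall that way, and a common threshold pulls a real benefit towards zero.
- A reader might see a contradiction with the Safety Population in the deletion sentence. It sits inside the Per Protocol bullet, and the Safety Population is defined separately, so this is a matter of wording.

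The pilot label lowers the consequence, but the stated objective is still a comparison with placebo. Deferring to an analysis plan not shown does not answer the point either, because the protocol itself names the efficacy set and orders the deletion.

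**Conclusion.** The point holds as a flaw in the choice of analysis set. The protocol makes a set formed after randomisation the sole basis for efficacy, and no other section supplies an analysis of all randomised subjects. The result would not be protected by randomisation and would describe a narrower population than the objective does.

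How much this matters numerically cannot be read from the protocol, which states no expected exclusion rate. Under the assumptions above, the consequence ranges from lost power alone, through attenuation of a true 0.5 SD effect to about 0.35 SD, to a spurious 0.15 to 0.34 SD difference with 9% to 23% rejection at the extreme. The last range is an illustration of one extreme, not a forecast.

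**What to change.** - In sections 8.2 and 8.3, make the primary efficacy analysis one of all randomised subjects as allocated, whatever their compliance, violations or Visit 2 attendance. Keep Per Protocol as supportive.
- State that the deletion of subjects below 80% compliance applies to the Per Protocol set only.
- Ask subjects who stop the supplement to complete the Visit 3 JKOM and JOA where they consent. This leaves every clinical withdrawal rule as it is.
- Replace list-wise deletion for JKOM and JOA with a prespecified method for missing Visit 3 scores, for example multiple imputation using arm, baseline score and the model covariates.
- Add a sensitivity analysis that assumes worse outcomes for subjects withdrawn for exacerbation. Such imputation treats missingness as unrelated to the unseen score given those variables, which is doubtful for these subjects.

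The cost is mostly wording, with no extra subjects. There is some effort in following up subjects who stop, and the consent text may need a sentence. The estimated effect may be smaller because non-compliers are included. The change should be made before unblinding, and early enough that Visit 3 scores can still be collected.

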# STUDY OBJECTIVES

To examine the effect of a 30 days (approximately 4 weeks) of krill oil administration on knee joint pain.

Primary outcomes**:**

- Japanese Knee Osteoarthritis Measure (JCOM)
- The Japanese Orthopedic Association knee rating score (JOA score)

Secondary outcomes**:**

- Blood and urine analysis
- Range of motion (ROM) of the knee

* ROM was deleted from the secondary outcome because of the difficulty to obtain the reliable data.

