***Statistical tests:***

Mean difference between independent groups will be analyzed by Student’s t test or Mann-Whitney U test.

Mean difference between paired groups will be analyzed by paired t test or Wilcoxon’s signed rank test.

For the primary outcomes, changes from baseline will be analyzed by generalized linear model controlling for age, sex, weight, and smoking (yes or no) and drinking (yes or no) habits. Every interaction will be tested and included if it decreases Akaike’s information criteria.

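### One blank JKOM item at either visit removes the subject from the JKOM primary analysis; a minimum-items scoring rule would avoid that loss of precision

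*Protocol*

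**What the plan says.** The analysis text under section 8.2 of the Protocol sets a general rule, "Missing values will be deleted in a pair-wise manner for the comparison", and then an exception for JKOM (questions 1 to 25) and JOA, for which "missing data will be deleted in a list-wise manner".

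Four other parts of the Protocol determine how the exception works:

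- **Study Objectives** names JKOM (spelled JCOM there) and JOA as the only primary outcomes.
- **JKOM and JOA** separates the two instruments by who completes them: "Subjects will fill JKOM questionnaire by his/her own", whereas "Orthopedist will fill JOA score list interviewing subject".
- **Statistical tests** says that for the primary outcomes "changes from baseline will be analyzed by generalized linear model controlling for age, sex, weight, and smoking", together with drinking. A JKOM result therefore needs a score at both Visit 1 and Visit 3.
- **Study Design**, **Removal by Qualified Investigator** and **section 8.2** set 25 subjects per arm, no replacement of subjects who leave early, and an efficacy analysis in the per-protocol set only.

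The Protocol gives no minimum number of answered items, no proration and no item-level imputation.

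**The concern.** List-wise deletion in its usual sense keeps a record only if every listed variable is present. Applied to the items of a multi-item total, it makes the score all-or-nothing: 24 answers out of 25 count the same as none. Because the endpoint is a change score, this condition must be met twice.

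The clause acts mainly on stray blanks. The per-protocol definition already requires completion of all visits, so subjects who miss a whole visit are out before it applies. What it then removes is largely subjects who took the supplement, attended and filled in nearly all of the form. They are lost on top of the per-protocol exclusions, and no reserve is described: early leavers are not replaced, and the sample size section mentions no dropout allowance. What is at stake is the precision of one of the two primary comparisons.

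**Working it through.** **Inputs from the Protocol.** 25 JKOM items (section 8.2); two visits (change from baseline, Statistical tests); 50 subjects, 25 per arm (Study Design).

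**Inputs assumed.** The per-item missing rate p, which the documents do not give. For the power figures only: two-sided 5% level, 80% power and a true difference of 0.8 SD. The Protocol states none of these. Its sample size rests on plasma EPA and DHA results from a previous krill oil study, so there is no planned power for JKOM to reproduce.

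**Step 1: independent blanks.** A subject is kept only if all 2 × 25 = 50 responses are present.

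Share lost = 1 − (1 − p)^50. For example, at p = 1%: 1 − 0.99^50 = 0.395.

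The standard error grows by 1/√(share kept), which needs no assumption about level or power. At p = 1%: 1/√0.605 = 1.29.

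| p per item | lost at one visit, 1 − (1 − p)^25 | lost over two visits | left of 50 | standard error multiplied by |
|---|---|---|---|---|
| 0.1% | 2.5% | 4.9% | 47.6 | 1.03 |
| 0.2% | 4.9% | 9.5% | 45.2 | 1.05 |
| 0.5% | 11.8% | 22.2% | 38.9 | 1.13 |
| 1% | 22.2% | 39.5% | 30.3 | 1.29 |

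A 20% loss needs p = 1 − 0.8^(1/50) = 0.45%.

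**Step 2: blanks that cluster within subjects.** Let each subject have their own blank rate, beta-distributed with mean p and intra-subject correlation ρ. With a = p(1 − ρ)/ρ and b = (1 − p)(1 − ρ)/ρ, the share lost is 1 − B(a, b + 50)/B(a, b), where B is the beta function. At p = 1%:

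| ρ | lost over two visits | standard error multiplied by |
|---|---|---|
| 0.05 | 22.1% | 1.13 |
| 0.1 | 16.0% | 1.09 |
| 0.3 | 7.5% | 1.04 |
| 0.5 | 4.4% | 1.02 |

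**Step 3: power, for orientation only.** By the normal approximation, the detectable difference is (1.960 + 0.842) × √(2/n per arm). With 25 per arm it is 0.79 SD. Under independence it becomes 0.90 SD at p = 0.5% (19.4 per arm) and 1.02 SD at p = 1% (15.1 per arm). Power for 0.8 SD goes from 81% to 70% and 60% respectively.

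**Step 4: what a 20-of-25 threshold would recover.** Under independence at p = 1%, the chance of six or more blanks at a visit is about C(25,6) × 0.01^6 × 0.99^19 = 177,100 × 10⁻¹² × 0.826 ≈ 1.5 × 10⁻⁷. Practically every subject lost in Step 1 would be kept. Under strong clustering there is less to recover, because fewer subjects are affected and some of them leave more than five items blank.

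**The case against.** The strongest reply is that the size of the loss is not in evidence. The documents give no item-missing rate. JKOM is listed among the assessments at two clinic visits, and omissions often concentrate in a few people. At p = 0.1%, or with strong clustering at p = 1%, the loss is about 5% and the standard error grows by 2% to 3%. This stands. A reader might infer that the rule will remove a large part of the trial, and the documents do not support that.

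Three further limits also stand.

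- **JOA.** A reader might carry the 25-item calculation over to JOA, or suppose that a blank JKOM item also removes the subject's JOA result. The 25 items are JKOM's alone, the orthopedist completes JOA by interview, its item count is not stated, and nothing says that a gap in one instrument deletes the other.
- **Bias.** A reader might infer a biased treatment comparison. Baseline blanks precede treatment, the trial is double-blind, and age, an obvious candidate for predicting skipped items, is a covariate in the primary model. Bias between arms would need post-baseline skipping related to both arm and outcome, and the documents point to no such mechanism.
- **The pair-wise contrast.** For a single measured variable, pair-wise deletion also drops a subject whose value is missing. The weakness is the lack of any partial-completion rule for a multi-item total, rather than a harsher rule chosen for the primary outcomes.

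It could also be said that scoring belongs in a statistical analysis plan. Here, however, the Protocol does not leave the matter open. It prescribes deletion, and a later plan that prorated items would depart from it.

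**Conclusion.** The point holds for JKOM as a question of precision. Read in its usual sense, the written rule discards a subject's JKOM change score for one blank among 50 self-completed responses, and no other section softens it.

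The size depends on an item-missing rate that has to be assumed. Under independence the loss runs from about 5% of subjects at 0.1% per item to 39% at 1%; at 1% it falls to about 4% to 22% for ρ from 0.5 to 0.05. It becomes material at roughly 0.5% per item or more if blanks are spread across subjects. These percentages apply to whatever per-protocol set remains, which may be smaller than 50.

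For JOA the same clause applies, but the loss cannot be quantified and is probably small. Neither a large loss nor bias between arms is shown. The change is worth making because it is cheap and protects primary data in a trial of 25 per arm with no replacement.

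**What to change.** In the Analysis Plan (section 8.3), replace list-wise deletion for JKOM with a prespecified minimum-items rule. For example:

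- If at least 20 of the 25 items are answered at a visit, prorate the total: sum of answered items × 25 / number answered.
- If fewer are answered, the visit score is missing and the subject is left out of that change-score comparison.
- Report the complete-case result as a sensitivity analysis.

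The threshold of 20 is a suggestion; the documents give no JKOM scoring source that fixes one. It should be set before unblinding. For JOA, state the item count and how a blank is handled; no threshold can be proposed from the documents.

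Under the Visit 1 and Visit 3 procedures, have existing site staff check the JKOM form for blanks before the subject leaves. This prevents most of the problem at source.

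The cost is a few sentences and a brief check at two visits. The downside is that proration assumes skipped items resemble the answered ones, which the complete-case analysis helps to probe.
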